#### Physiotherapy plus telephone coaching

The physiotherapy intervention will be the same as for the physiotherapy only group and delivered by the same physiotherapists. The participants in this group will also receive a telephone coaching intervention aimed at improving their adherence to their home exercise program and increasing their levels of general physical activity through behaviour change support. They will receive additional written information that explains the behaviour change support process. Telephone coaching sessions will be delivered 6–12 times during the 6-month intervention period. Calls will occur in weeks 2, 4, 8, 13, 21 and 25. Up to six additional calls can be made at any time during the 6 months according to participant confidence in taking action to change physical activity behaviours, adherence level, and preferences, as determined by the telephone coach, physiotherapist and participant. The initial call length is expected to range between 30–45 minutes with the remaining call durations lasting between 15 and 30 minutes.

The behaviour change model used for the telephone coaching intervention is the HCA Model of Health Change (http://www.healthchangeaustralia.com/the-hca-model.htm). Health Change Australia has been providing professional development training and consultancy in using the HCA Model of Health Change in Australia (since 2006) and Canada (since 2010). They have trained over 5,000 health professionals who work in a variety of public and corporate health settings. The HCA model has been used by both private and state based organisations to provide telephonic coaching services.

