### Economic Evaluation

The economic evaluation will assess the incremental cost of the physiotherapy plus telephone coaching intervention compared with physiotherapy only. The primary economic evaluation will report cost effectiveness at 18 months with secondary economic evaluations at 6 and 12 months. The incremental cost will be compared to the incremental benefits of treatment in terms of a clinically significant improvement in pain, a clinically significant improvement in function, and the difference in quality adjusted life years (QALYs). The incremental QALYs will be measured by the between group difference in the mean AQoL2 score over 6, 12 and 18 months. A social perspective on costs will be taken and will include resource use incurred both by health services and by the patient irrespective of payment source. Prospective self-reported direct health care use will be collected every 3 months using log sheets. Health care costs will be calculated from the utilisation data and published average unit costs for each item. The direct cost of the intervention will be based on physiotherapy charges per session and telephone coaching costs per person. The inclusion of time/productivity gains is controversial and the cost effectiveness ratios will be calculated with and without these “indirect costs”. Confidence intervals for incremental cost effectiveness will be calculated directly using non parametric bootstrapping. In addition we will calculate a cost effectiveness acceptability curve based for a range of hypothetical money values of outcomes [74]. This will be done using individual cost and outcome data over the 6, 12 and 18 months or, if adjustments for imbalance at baseline are necessary, using regression analysis [75]. As part of the economic evaluation we will survey participants at the 6, 12 and 18 month questionnaire about their satisfaction with the intervention including its value for money.

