### Sample size

The primary endpoints will be change from baseline to 6 months in (i) knee pain (NRS) and (ii) physical function (WOMAC). The minimum clinically important difference to be detected in OA trials is a change in pain of 1.8 units on NRS [76] and a change in physical function on WOMAC of 6 units (out of 68) [77]. Randomisation is stratified by physiotherapist and hence no clustering effects of participants within physiotherapists need be accounted for. However, there may be clustering effects due to participants treated by the same telephone coach in the physiotherapy plus telephone coaching arm which we account for as follows: With three telephone coaches, one third of the participants in the physiotherapy plus telephone coaching arm are expected to be treated by each coach, and we assume in the sample size calculation an intra-cluster correlation of 0.05, which has been demonstrated to be conservative for patient-level outcomes across health care practices [78]. Based on combined data from our 12 month RCT in 200 people with knee OA [79] and our 12 week RCT in 76 people with knee OA who undertook a hip strengthening program [22], we assume a between-participant standard deviation of 2.2 for pain and 11.6 for WOMAC physical function, and a baseline to 6-month correlation in scores of 0.29 for pain and 0.51 for physical function. These assumptions, together with an analysis of covariance adjusted for baseline scores and for clustering, produce a sample size of 67 patients per intervention arm to achieve 80% power to detect the above differences. Allowing for a 20% attrition rate we will recruit 84 patients per arm, or 168 patients in total.

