### Data and statistical analysis

A biostatistician (AF) will oversee the blinded analyses of the data. Main comparative analyses between groups will be performed using an intention-to-treat analysis. To account for missing data, multiple imputation of missing follow-up measures, assuming missing data are missing at random and follow a multivariate normal distribution [80] will be performed as a sensitivity analysis. For continuous outcome measures, differences in mean change (baseline minus follow-up) will be compared between groups using linear regression random effects modelling adjusted for baseline values of the outcome and clustering effects of telephone coaches. Model diagnostic checks will utilise residual plots. Similar regression models for binary and ordinal outcome measures will use random effects logistic and proportional odds models, respectively. Estimates of intervention effects under hypothetical full adherence will be performed using recently developed methods based on causal modelling ideas [81] which we have successfully applied to data from our recently completed knee OA trial [79].

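### Baseline adjustment in the economic analysis depends on an undefined finding of imbalance; it should be fixed in advance, and the handling of coach clustering stated

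*Protocol article*

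**What the plan says.** The Economic Evaluation section of the protocol article sets the primary cost-effectiveness analysis at 18 months, with secondary analyses at 6 and 12 months. Benefits are clinically significant improvement in pain, the same in function, and QALYs taken from the between-group difference in mean AQoL2 score. On uncertainty it says: "Confidence intervals for incremental cost effectiveness will be calculated directly using non parametric bootstrapping". An acceptability curve follows, and the default route is then described: "This will be done using individual cost and outcome data over the 6, 12 and 18 months". The same sentence offers a second route, which applies only on a condition: "if adjustments for imbalance at baseline are necessary, using regression analysis". No trigger for necessity is given, no covariates are named, and neither the resampling unit nor the telephone coach is mentioned.

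The Data and statistical analysis section has no such condition for continuous clinical outcomes. They are compared by "linear regression random effects modelling adjusted for baseline values of the outcome and clustering effects of telephone coaches". The Sample size section says that "there may be clustering effects due to participants treated by the same telephone coach in the physiotherapy plus telephone coaching arm" and allows for them: "we assume in the sample size calculation an intra-cluster correlation of 0.05". Table 1 lists AQoL2 at month 0, so the baseline covariate will be available.

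**The concern.** The article specifies two estimators for the same quantity and chooses between them after the baseline data are seen, on an undefined criterion. Baseline utility can be expected to predict follow-up utility, so an analysis that leaves it out is less precise. It is also off-target in a trial where a chance baseline difference exists but is not considered large enough to act on. With no criterion, two analysts could reach different cost-effectiveness results from the same data without departing from the protocol. The cost-effectiveness hypothesis (H4) rests on this analysis.

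Second, the same participants and the same three coaches generate the economic data, and two of the three benefit measures are built on pain and function, the outcomes for which the sample size allows clustering. Costs may cluster too: "Up to six additional calls can be made at any time during the 6 months", and the coach takes part in deciding them. The economic section does not say whether its intervals and acceptability curve reflect this.

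**Working it through.** **1. The plan's own figure.** The article gives no figure for the economic analysis, so the sample size is reproduced to confirm the clustering allowance. Inputs from the Sample size section: difference 6, SD 11.6, correlation 0.51 (function); difference 1.8, SD 2.2, correlation 0.29 (pain); power 80%; intra-cluster correlation (ICC) 0.05; three coaches in one arm. Two-sided alpha of 0.05 is assumed.

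- Before clustering: n = 2 × (SD × 2.80 / difference)² × (1 − r²). Function gives 43.4 per arm, pain 21.5.
- With clustering in the coaching arm only: multiply by the mean of 1 and 1 + (n/3 − 1) × 0.05, and iterate. Function gives 66.3, so 67; pain gives 25.5, so 26.
- Attrition: 67 / 0.8 = 83.75, so 84 per arm and 168 in total.

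All stated figures reproduce. Function sets the size, and the clustering allowance takes it from 43.4 to 66.3.

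**2. Precision given up by not adjusting.** Adjustment multiplies the variance by 1 − r², so the reduction is r². The protocol gives no AQoL2 correlation; 0.51 is borrowed from function.

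| Assumed r | Variance reduction |
|---|---|
| 0.30 | 9% |
| 0.51 | 26% |
| 0.70 | 49% |

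**3. Behaviour of the conditional rule.** Simulation of 40,000 trials: 67 per arm, normal outcome, no treatment effect, no clustering. Because the protocol gives no trigger, adjustment was applied when the baseline difference had p < 0.05.

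| Assumed r | Mean error (SD units) | Coverage of 95% interval | Average SE: conditional / always adjusted |
|---|---|---|---|
| 0.30 | −0.0003 | 95.3% | 0.1722 / 0.1651 = 1.04 |
| 0.51 | −0.0012 | 95.7% | 0.1714 / 0.1489 = 1.15 |
| 0.70 | 0.0009 | 96.5% | 0.1703 / 0.1237 = 1.38 |

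There is no bias on average and no undercoverage. The cost is width.

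**4. When an imbalance is left unadjusted.** Take a baseline difference of 1.9 standard errors, just short of that trigger. The unadjusted estimate is then shifted by r × 1.9 of its own standard errors, with conditional SD √(1 − r²). At r = 0.51 the shift is 0.97 and the SD 0.860. Coverage given that imbalance is Φ((1.96 − 0.97)/0.860) − Φ((−1.96 − 0.97)/0.860), about 87.5%. It is about 92% at r = 0.3 and 81% at r = 0.7.

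**5. Clustering, if individuals are resampled.** The coaching-arm design effect is DE = 1 + (67/3 − 1) × ICC. The true SE exceeds the individual-level SE by √((1 + DE)/2), and coverage is 2Φ(1.96/ratio) − 1. No ICC is given for costs or QALYs, so a range is shown.

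| Assumed ICC | DE | SE ratio | Coverage |
|---|---|---|---|
| 0.01 | 1.213 | 1.052 | 94% |
| 0.02 | 1.427 | 1.102 | 92.5% |
| 0.05 | 2.067 | 1.238 | 89% |

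**6. Price of allowing for coach.** With three coaches, the coaching-arm mean has 2 degrees of freedom between coaches. At ICC 0.05, Satterthwaite gives (1 + 2.067)² / (1²/66 + 2.067²/2) ≈ 4.4 df and t ≈ 2.69. The interval is then 2.69 × 1.238 / 1.96 ≈ 1.7 times the individual-level width.

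**The case against.** A reader might infer that the economic intervals are biased and too narrow. The documents do not support that. Randomisation keeps the unadjusted difference unbiased on average, and under the rule tested the intervals were slightly conservative. The conditional rule makes intervals wider; only clustering could make them too narrow.

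A reader might also take a baseline AQoL2 difference of 0.04 and carry it forward as 0.04 × 1.5 years = 0.06 QALY. That assumes complete persistence. At a correlation of 0.51 the carry-over is 0.04 × 0.51 × 1.5 ≈ 0.031. It also uses a difference equal to the article's clinically important one, which the clause would probably catch. Nor does the article say that baseline utility forms part of a QALY area.

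On clustering, the case against is strong. Individual-level resampling is the natural reading but is not stated, and the regression route does not exclude coach. Such detail is commonly left to a full analysis plan, so its absence is not an error in itself. The ICC of 0.05 is described as conservative and concerns patient-level outcomes. AQoL2, as a continuous secondary outcome, is already covered by the clinical model with coach effects, so what is open is costs and joint uncertainty. Extra calls are decided by coach, physiotherapist and participant together, and coaches are allocated at random. Random allocation makes the coaches' caseloads comparable but does not remove differences between coaches.

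What the objection does not remove is the adjustment clause. It is a stated rule, not an omission, so a later analysis plan would have to replace it.

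**Conclusion.** The point holds as a matter of precision and prespecification. The economic analysis ties baseline adjustment to an undefined condition, while the clinical analysis adjusts always. Relative to always adjusting, the conditional rule makes the average standard error about 4%, 15% or 38% larger at assumed correlations of 0.3, 0.51 or 0.7. These figures rest on a borrowed correlation, an assumed trigger and a normal outcome. They apply to QALYs; the gain for net benefit also depends on how much of its variance comes from costs. The rule also leaves discretion to the analyst, and the estimate is off-target in any trial where an imbalance goes unadjusted.

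Clustering is a secondary point. If individuals are resampled, the loss of coverage is about one percentage point at an ICC of 0.01 and about six at 0.05. Neither the resampling unit nor an ICC for costs or QALYs is stated, so this is a matter to settle, not a demonstrated fault.

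**What to change.** Delete the conditional phrase in the Economic Evaluation section. State that incremental QALYs and net benefit will always be estimated by regression with baseline AQoL2 as a fixed covariate, whatever the observed balance, and that the acceptability curve will be drawn from that model. Bootstrapping can stay if the regression is refitted in each resample.

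State how coach is handled, and report the economic intervals also with coach clustering in the coaching arm allowed for, at least as a sensitivity analysis. A plain bootstrap of three coaches would be unreliable; a coach effect with small-sample degrees of freedom is preferable. The report should say that three coaches give few degrees of freedom and that these intervals will be markedly wider, about 1.7 times the individual-level width at an ICC of 0.05.

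The cost is a change of wording and modest extra modelling. No new data are needed, because AQoL2 is already collected at baseline.

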### Sample size

The primary endpoints will be change from baseline to 6 months in (i) knee pain (NRS) and (ii) physical function (WOMAC). The minimum clinically important difference to be detected in OA trials is a change in pain of 1.8 units on NRS [76] and a change in physical function on WOMAC of 6 units (out of 68) [77]. Randomisation is stratified by physiotherapist and hence no clustering effects of participants within physiotherapists need be accounted for. However, there may be clustering effects due to participants treated by the same telephone coach in the physiotherapy plus telephone coaching arm which we account for as follows: With three telephone coaches, one third of the participants in the physiotherapy plus telephone coaching arm are expected to be treated by each coach, and we assume in the sample size calculation an intra-cluster correlation of 0.05, which has been demonstrated to be conservative for patient-level outcomes across health care practices [78]. Based on combined data from our 12 month RCT in 200 people with knee OA [79] and our 12 week RCT in 76 people with knee OA who undertook a hip strengthening program [22], we assume a between-participant standard deviation of 2.2 for pain and 11.6 for WOMAC physical function, and a baseline to 6-month correlation in scores of 0.29 for pain and 0.51 for physical function. These assumptions, together with an analysis of covariance adjusted for baseline scores and for clustering, produce a sample size of 67 patients per intervention arm to achieve 80% power to detect the above differences. Allowing for a 20% attrition rate we will recruit 84 patients per arm, or 168 patients in total.

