### Intervention providers

Thirteen physiotherapists who have at least 2 years post-graduate musculoskeletal experience and work in private clinics in metropolitan and regional Victoria will provide the physiotherapy intervention. Physiotherapists were chosen to deliver the physical activity intervention as they have expertise in exercise prescription and are key providers of structured physical activity in the community for people with knee OA. A clinical practice survey in the United Kingdom has shown that 100% of physiotherapists utilized exercise for this patient group [43].

Three registered nurses who complete training and mentoring from Health Change Australia to develop skills in providing behaviour change support will provide the telephone coaching for the study. None of the nurses will have training or experience in health behaviour change support or telephone coaching prior to involvement with this study.

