Our study is the first RCT to investigate the effect of a telephone coaching intervention to specifically support a physiotherapist-delivered physical activity intervention on pain and function in people with knee OA. Strengths of the study design are the pragmatic nature of treatment delivery by practicing physiotherapists in community physiotherapy clinics, and by health practitioners trained in the HCA model of Health Change, as well as the reproducibility of both the physiotherapy and telephone coaching programs. These features will improve the ability to translate the findings into a range of interdisciplinary health care settings and enable future researchers to replicate the behaviour change intervention. Importantly the physical activity program is individualised with regard to the content and intensity level of the home exercises and the plan for increasing daily levels of physical activity. The study is designed so as to conform to CONSORT requirements for non-pharmacological interventions. It is adequately powered for our primary outcome measures and our recruitment strategy will result in a well-characterised sample from both metropolitan and regional areas. In addition, our study includes longer-term follow-up and primary outcomes recommended by international osteoarthritis researchers and which are of relevance to the recipients of the intervention.

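### The 80% power for WOMAC function treats the between-coach variance as known; estimated from three coaches at the protocol's ICC of 0.05, power is about 60%, and about 72% at best among the 5% tests computed

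*Protocol article*

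**What the plan says.** All references are to the protocol article.

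- **Sample size.** The primary endpoints are 6-month changes in pain and WOMAC function. The differences to detect are "a change in pain of 1.8 units on NRS" and 6 points on the 0–68 function scale. On variability, "we assume a between-participant standard deviation of 2.2 for pain and 11.6 for WOMAC physical function", with "a baseline to 6-month correlation in scores of 0.29 for pain and 0.51 for physical function". Coach clustering is allowed for in the coaching arm only, with three coaches of equal load and an ICC of 0.05 that the section calls conservative. With ANCOVA, these inputs "produce a sample size of 67 patients per intervention arm to achieve 80% power to detect the above differences". Attrition of 20% raises 67 to 84 per arm, 168 in total.
- **Intervention providers.** The coaches are "Three registered nurses who complete training and mentoring from Health Change Australia", so the number of clusters is fixed at three.
- **Data and statistical analysis.** Continuous outcomes are compared with a random effects linear model "adjusted for baseline values of the outcome and clustering effects of telephone coaches". No reference distribution or degrees of freedom are given.
- **Discussion.** Of the trial it says: "It is adequately powered for our primary outcome measures".

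**The concern.** A design-effect formula with normal quantiles assumes that the variance of the treatment contrast is known, or is estimated from many clusters. Here about two thirds of that variance (2.07 parts of 3.07, see the working) comes from the coaching arm, where the information on it is the spread of three coach means. A test that respects this needs a critical value well above 1.96, and power falls. A test that ignores it comes closer to the stated power but rejects too often.

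Function is the endpoint that sets the sample size, and the primary hypothesis names it alongside pain. A null function result read against 80% power would be taken as stronger evidence of no effect than it is. A function p-value just below 0.05 from a normal test would be trusted too much.

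**Working it through.** **Inputs (Sample size section).** Function: difference 6, SD 11.6, correlation 0.51. Pain: difference 1.8, SD 2.2, correlation 0.29. ICC 0.05, three coaches in one arm, 67 analysed per arm. Assumed: two-sided alpha of 0.05, and the ICC applied to the baseline-adjusted variance. This reading reproduces the stated 67.

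**Step 1: reproduce the plan.**
- Residual SD = 11.6 × √(1 − 0.51²) = 9.98.
- Coaching-arm design effect D = 1 + (67/3 − 1) × 0.05 = 2.07.
- SE = 9.98 × √[(1 + 2.07)/67] = 2.135.
- Difference/SE = 6/2.135 = 2.81.
- Normal power = Φ(2.81 − 1.96) = 80.3%. At 66 per arm it is 79.9%, so 67 is the first size to reach 80%.
- 67/0.8 = 83.75, so 84 per arm.
- For pain, residual SD = 2.2 × √(1 − 0.29²) = 2.105, SE = 0.450, ratio 4.00 and normal power 97.9%. Function is the limiting endpoint.

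**Step 2: degrees of freedom.** The control-arm variance rests on 66 df and the coaching-arm variance on 2. Satterthwaite:

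df = (1 + D)² / (1/66 + D²/2) = 3.07² / (0.015 + 2.136) = 4.37.

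The two-sided 5% critical value of t is 2.69. Noncentral t power is 58.8% for function and 86.2% for pain.

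**Step 3: simulation.** 400,000 trials with 67 per arm, three equal coaches in the coaching arm, and a REML fit with the coach variance bounded at zero. Results for function at ICC 0.05:

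| Test | Type I error | Power |
|---|---|---|
| True variance known, 1.96 | 5.0% | 80.3% |
| REML, normal reference | 7.4% | 78% |
| REML, Satterthwaite df | 5.2% | 60% |
| REML, critical value about 2.18, calibrated at this ICC | 5.0% | 72% |

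The coach variance is estimated as zero in about 37% of trials. For pain at ICC 0.05, power is 82% with Satterthwaite df and 94% with the calibrated value. If all 84 per arm were analysed, Satterthwaite power for function would be 63%.

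**Step 4: dependence on the ICC (function, 67 per arm, Satterthwaite df).**

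| ICC | Power |
|---|---|
| 0.05 | 60% |
| 0.02 | 71% |
| 0.01 | 76% |
| 0 | 81% |

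At ICC 0.01 and 0 the Satterthwaite test is conservative (type I error 3.8% and 3.3%), and the plain normal test at ICC 0.01 has about 4.9%.

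**The case against.** **The arithmetic is right.** It is: 67, 84 and 168 all follow from the stated inputs, and the clustering is placed in the correct arm. The fault is the approximation used, not a slip.

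**Degrees of freedom belong in the analysis plan.** Largely true, and their absence from an article is no finding in itself. The 80% is different, because it is a stated property of the design and the Discussion repeats it in general terms.

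**Satterthwaite is one method among several.** This stands. A critical value of 2.18 on the same statistic holds 5% or less at the ICCs checked from 0 to 0.05 and gives about 72% for function at 0.05. The loss at the planning ICC is therefore about 8 points at the least and about 20 with Satterthwaite, but every 5% test computed falls short.

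**The ICC is conservative.** If the true value is lower, the gap narrows. A test calibrated at each ICC reaches 80% at 0.03, 84% at 0.02 and 88% at 0.01. But the protocol's claim is made at 0.05, and the support it cites concerns health care practices, not individual coaches.

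Three stronger readings are tempting and not supported:
- *The planned analysis has 7% type I error.* The protocol names no normal test, so this is conditional.
- *No number of patients could give adequate power with three coaches.* A ceiling near 70% appears only with Satterthwaite at ICC 0.05. The calibrated test reaches 82% at 130 per arm.
- *The trial is underpowered for both primary outcomes.* Pain keeps at least 80% at ICC 0.05 under each method computed.

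**Conclusion.** The stated 80% power for function does not hold at the protocol's own ICC of 0.05 once the coach variance is estimated from three coaches. It is about 60% with REML and Satterthwaite degrees of freedom, and about 72% with a critical value calibrated to 5% at that ICC. Pain is not affected to the point of falling below 80%.

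This rests on a two-sided 5% level (not stated), equal coach loads, the protocol's SDs and correlations, and the ICC applied to the baseline-adjusted variance. The shortfall shrinks with the ICC and largely disappears at 0.01 or below. The matter is a misstated power figure and an analysis that needs a small-sample reference. It does not invalidate the design.

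**What to change.** 1. **Sample size and Discussion.** Restate function power at 67 per arm as about 60% (Satterthwaite df, ICC 0.05, three coaches) and at most about 72% for a test calibrated to 5%. Show the ICC range (71% at 0.02, 76% at 0.01, 81% at 0). State pain as at least 80%. State the significance level. Remove the unqualified claim of adequate power as it applies to function.
2. **Data and statistical analysis.** Say that the coach random effect is fitted in the coaching arm only, which matches the Sample size section, and that tests and intervals use small-sample degrees of freedom (Satterthwaite or similar).

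**Cost.** Wording only, with no change to the number of patients or coaches. Intervals will be wider, the stated power is less favourable, and the test will be somewhat conservative if the true ICC is near zero.
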